### Research Goals

The overall goal of the present study is to compare the efficacy of two dietary intervention approaches on weight loss and improving dietary quality among patients with the metabolic syndrome. One approach is complex and the other is simple. The two approaches are: 1) the AHA Dietary Guidelines [40] that is currently recommended to patients with the metabolic syndrome [41,42]; and 2) a high fiber diet that provides instruction on a single area of diet, fiber. Secondary research goals include examining changes in components of the metabolic syndrome, inflammatory markers, low-density lipoprotein (LDL-C) cholesterol levels, insulin levels, and glycosolated hemoglobin (HbA1c). We hypothesize that the high fiber condition will significantly improve overall diet quality and metabolic health over the AHA condition. Additionally, potential mediators (i.e., adherence and perceived ease of the diet) of the intervention effect at 12 months will also be examined.

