### Sample Size Consideration

The required numbers of patients for each arm were based on the primary outcome measure: change in body weight. Sample size was calculated using the method developed by Frison and Pocock [53] and implemented in Stata SE 10 (College Station, Texas, USA). Parameters used in sample size calculations were estimated in our pilot trial and historical data from metabolic patients in our clinics, and we assumed complete randomization of the study subjects to each treatment arms. With 95 complete cases per arm, the hypothesized difference in change in body weight (3.5 lbs) between the arms can be detected with >80% power at 5% significance level.

Considering possible attrition rate of 20%, the number of subjects in each arm should be not less than 120 subjects. Thus, a total of 240 patients will be enrolled in the study.

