### Statistical Analytic Approach for Primary Aim

The high fiber condition is hypothesized to induce greater weight loss than the AHA condition. We will evaluate the intervention effects on change in body weight using general and generalized linear latent and mixed models (GLLAMM) that have been implemented in Stata SE 10 [54,55]. The commonly used linear mixed models are a subgroup of GLLAMM. In the analysis, each patient is assumed to be independent. First, we will carefully evaluate the covariance structure of the outcome variables across time points, and test whether intervention may induce changes in variability in the outcomes. Proper covariance structure will be identified and prescribed in the final analysis. The participant identifier will be included as random effect, time and group as fixed effect. Treatment effect will be tested using time*group interactions in the models.

The analysis will adjust for potential confounders for weight change, including age, gender, baseline BMI, marital status, education attainment, physician advice regarding weight loss and other nutritional advice exposure prior to and during the trial. We also will evaluate the possible interactions between the intervention indicator and these patient's attributes to assess the presence of differential intervention effects among these subgroups. Session attendance will also be included in the models to determine whether this is a dose-response relationship between number of session attended and the extent of weight loss. Statistical approaches to secondary outcomes are very similar, and thus not discussed in detail.

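### Advice received during the trial is listed as a confounder in the primary analysis, and session attendance is not kept apart from the treatment test; both arise after randomisation and can bias the estimate

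*Protocol article*

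**What the plan says.** The Protocol article, section Sample Size Consideration, bases the trial on the "primary outcome measure: change in body weight", with a target difference between arms of 3.5 lb. The section Statistical Analytic Approach for Primary Aim specifies a mixed model over the visits, with participant as random effect, and tests treatment by the time-by-group interaction.

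That section then names the potential confounders to be adjusted for. Most are baseline attributes (age, gender, baseline BMI, marital status, education), but the list ends with "physician advice regarding weight loss and other nutritional advice exposure prior to and during the trial". The next sentence plans interactions between the intervention and these attributes, to look for differential effects among subgroups. After that comes: "Session attendance will also be included in the models to determine whether this is a dose-response relationship". Secondary outcomes are to be handled in much the same way.

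Mediation is announced separately, under Research Goals: "potential mediators (i.e., adherence and perceived ease of the diet) of the intervention effect at 12 months will also be examined". Table 1 lists session attendance as a process variable with a single mark at 12 months.

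**The concern.** A confounder of a treatment comparison must influence who gets which treatment. Randomisation fixes that before any trial-period advice is received or any session attended, so neither variable can confound it. Either may instead be a consequence of the assigned diet or of early weight loss. Participants who are not losing weight may seek outside advice, and those who are losing may keep attending.

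The article's own rationale makes arm differences plausible. It expects the simpler message to be easier to follow than the AHA guidelines. The AHA arm also receives calorie goals, while dietitians in the fiber arm are trained to leave calories and macronutrients aside.

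Conditioning on such a variable can remove part of the effect of assignment. It can also open a path through motivation, which drives both the covariate and weight change. The 3.5 lb on which the trial is sized is the difference between the arms as assigned, and the adjusted coefficient may then be a different quantity. A subgroup defined by advice received during the trial has a further problem: membership may itself depend on treatment.

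**Working it through.** **The plan's own figures.** The inputs are "With 95 complete cases per arm", 20% attrition and 3.5 lb. Enrolment: 95 / (1 - 0.20) = 118.75, so 119 per arm; the stated 120 is consistent. The stated power cannot be reproduced because no SD or correlation is given. Solving for the SD that gives exactly 80% power, two-sided 5%:

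SD = 3.5 / [(1.960 + 0.842) × √(2/95)] = 3.5 / (2.802 × 0.1451) = 8.61 lb

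The one-sided equivalent is 9.70 lb. The 8.61 lb serves only as a scale for what follows; no sample-size figure is disputed.

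**A model of weight change.** Negative values mean more loss in the high fiber arm. Let Δ be the arm difference in the post-randomisation covariate and s the within-arm slope of weight change on it. Then

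adjusted effect = effect of assignment - Δ × s

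Assumptions, none of them from the document: a covariate with SD about 1; a true effect of -3.5 lb; and three values of s. These are -3 lb per SD if the covariate itself acts on weight; 0.5 × (-3) = -1.5 if an unmeasured motivation drives both; and -4.5 if both hold.

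| Δ (SD) | s = -3 | s = -1.5 | s = -4.5 |
|---|---|---|---|
| +0.4 | -2.3 | -2.9 | -1.7 |
| +0.2 | -2.9 | -3.2 | -2.6 |
| 0 | -3.5 | -3.5 | -3.5 |
| -0.2 | -4.1 | -3.8 | -4.4 |
| -0.4 | -4.7 | -4.1 | -5.3 |

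Simulation with 400,000 participants per scenario agreed: adjusted estimates ran from -5.3 to -1.7 lb, and those without the covariate stayed at about -3.5. With a true effect of zero, the adjusted estimates ran from -1.8 to +1.8 lb, so a spurious difference is also possible. Where Δ was 0, the bias was about 0.

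**The mixed model that the article states.** One simulated data set of 4,000 participants, visits at 0, 3, 6 and 12 months, a random intercept, true 12-month effect -3.5 lb, Δ = +0.4 and s = -4.5:

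| How the covariate enters | 12-month time-by-group estimate (lb) |
|---|---|
| Not included | -3.36 (SE 0.20) |
| Time-constant main effect | -3.36 |
| Interaction with time | -1.72 |
| Time-varying covariate | -1.71 |

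A second set of runs used 120 per arm, 60 replicates, one more session attended in the fiber arm, and motivation driving both attendance and weight change. The estimate was -3.59 without attendance and -3.59 with it as a main effect. With about 23% attendance-related dropout it was -3.54 and -3.54. It moved to about -2.65 only when attendance also interacted with time.

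**Which form does the article intend?** It does not say. A dose-response on the extent of weight loss would need an attendance-by-time term or weight change as the outcome, and both are distorting forms. Advice received during the trial changes over follow-up, so it would naturally be time-varying.

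**The case against.** The strongest reply concerns attendance. It is not in the list of adjustment variables. It comes after that list and after the sentence on interactions, with its own stated purpose, so it may be meant as a supplementary model. The article is condensed, and its silence on a separate primary model proves little. Both arms are offered the same 11 sessions, with make-ups for those missed, so a large arm difference is not implied. Adherence and perceived ease, not attendance, are the named mediators.

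Much of this stands. What remains is that the sentence puts attendance in the models, and the treatment test is described in the same terms, with nothing to separate the two. The defence does not reach advice received during the trial, which is named outright for adjustment.

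Three stronger readings are tempting, and the documents do not support them:

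- A reader might infer that the primary model no longer estimates the effect of assignment. That holds only for some model forms and only if the covariate differs by arm.
- A reader might infer a definite loss. For example, 1 lb per session and one extra session give -3.5 + 1.0 = -2.5 lb, and power near 52% at a standard error of 8.61 × √(2/95) = 1.25 lb. Both inputs are assumed, and the sum belongs to a change-score regression, not to the stated mixed model.
- A reader might infer that attendance is tested as an effect modifier. It is introduced only after that sentence. Within the list, only the advice received during the trial is open to the objection.

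**Conclusion.** The concern holds in conditional form. The article names one post-randomisation variable as a confounder in the analysis of the primary aim, carries it into the effect-modifier tests, and leaves a second one unseparated from the treatment test. The estimate can be biased in either direction if three things hold together: the variable is related to weight change; assignment affects it so that the arms differ; and it enters as time-varying, in interaction with time, or in a model of weight change. If it enters only as a time-constant main effect, the time-by-group estimate is essentially unaffected.

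Neither direction nor size can be derived from the document. The illustrative shift of up to about 1.8 lb, roughly half of the 3.5 lb design difference, rests on the assumed slopes, the assumed arm differences of up to 0.4 SD and the back-calculated SD. The case is firm for advice received during the trial. For attendance it is a matter of unclear wording. Because the point touches the primary estimate and is so cheap to settle, it should be settled before analysis.

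**What to change.** - Limit the advice item in the covariate list to advice received before randomisation, so that every adjustment variable in the primary model is fixed by then.
- Apply the same limit to the effect-modifier tests, and carry both limits over to the secondary outcomes.
- Report physician and nutritional advice received during the trial descriptively, by arm.
- State that the attendance dose-response is a separate, exploratory, non-causal analysis that does not enter the primary treatment test.

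The cost is wording only. No data item is dropped, the sample size is unaffected, and the attendance question is kept.

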### Project Management and Participant Tracking

Under the direct leadership of the project director, project staff will be responsible for: 1) tracking patients to ensure that all necessary data are collected in a timely fashion; 2) assist with developing monitoring reports; 3) providing timely and relevant feedback to the leadership regarding the accuracy of data; and, 4) the day-to-day functioning of the study across all 10 waves of recruitment, intervention and assessment. The tracking system used for monitoring patient activities and providing necessary prompts based on a communication system using Lotus Notes from IBM (Lotus Notes R5.0.11^®^). Multiple levels of password protection are utilized to ensure data security. The tracking system will facilitate timely scheduling of assessments and identification of completed assessments.

### Data Entry and Management of Data Files

All data are entered into computerized data files (Epi Info for double-entry and Lotus Notes for patient tracking). All data entry systems employ automatic checks for values that are out of range or represent errors of faulty logic. Each patient will be assigned a study ID number to ensure confidentiality.

The data manager/programmer, under the supervision of the PI and project biostatistician will: 1) train project staff; 2) monitor all data collection protocols to assure compliance; 3) generate monitoring reports; 4) provide feedback regarding data accuracy and precision; and 5) implement variable edit checking. The study biostatistician will have responsibility for structuring the primary datasets, data linking procedures, variable naming conventions, codebooks, and documentation. Frequent exploratory analyses and range/value checking protocols will detect erroneous values. Data from each source will be merged using study-specific patient identification numbers and will be transferred to Stata SE 10 data files for analysis. All patient identifiers will be removed from analytic datasets. All database files will be stored on a password protected network drive with firewall protection that is managed by UMMS Information Service. All project-related data files will be automatically backed up daily per UMMS data safety protocol. A study directory will be established as the central repository for all final Stata datasets. Only the authorized project staff will have access to the databases. Project staff are prohibited to download data files with patient identifies to local drives unless authorized by the PI and Project Director.

## Discussion

Identifying a simpler dietary recommendation for weight loss and improving both dietary quality and metabolic health may demonstrate potential for a simple public health message to impact the metabolic syndrome and its sequelae of chronic disease. In a randomized clinical trial design, the present study will compare the efficacy of two intervention approaches to dietary change for CVD and diabetes prevention among persons with metabolic syndrome.

The prevalence of the metabolic syndrome is 26.7% according to the NHANES 1999-2000 survey of U.S. adults. Using 2000 census data, about 47 million US residents have the metabolic syndrome [4]. The metabolic syndrome is a harbinger of type 2 diabetes and CVD, both leading causes of mortality in the US. Lifestyle change is the cornerstone of recommended care for patients with metabolic syndrome [40,43].

Zivkovic and colleagues, in a comparative review of current dietary guidelines, diets, and dietary components, suggested that the AHA dietary recommendations are suitable for patients with the metabolic syndrome [41], with a similar suggestion made in a literature review, by Feldeisen and Tucker [42]. Theoretically, perfect adherence to the AHA diet would result in very high dietary quality and would impact components of the metabolic syndrome, however, progress in following this diet has been less than stellar. The composite of 13 different recommendations may be too complex for patients to understand and follow [6,9], limiting the benefits. The current study hypothesizes that it may not be necessary to give people guidance on every area of diet for diet quality to improve, because change in one area often result in changes in other areas of diet, both intentionally and unintentionally.

In a editorial on role of diet on insulin sensitivity and diabetes prevention, Xavier Pi-Sunyer recommended concentrating on educating the public to increase dietary fiber intake because "there is excellent evidence that the higher-fiber foods, made up of whole grains, fruits, and vegetables, will do people good"[20]. Although evidence demonstrates a link between dietary fiber, body weight and metabolic syndrome, more research is necessary to translate epidemiologic evidence and recommendations into effective clinical practice. To further this goal, the proposed study will measure inflammatory markers to elucidate possible mechanisms by which dietary fiber alone can impact metabolic syndrome, as compared to the more complex approach currently recommended by the AHA.

In addition to improving markers of metabolic syndrome, high intake of dietary fiber is associated with improved diet quality. In an observational study, Kranz and colleagues found that children in the high-fiber quartile consumed diets with higher nutrient density and increased number of servings from Food Guide Pyramid food groups (i.e.; fruit and vegetables, whole grains) [56]. Consumption of whole grain carbohydrates increased and the percentage of calories from fat significantly decreased; intake of micronutrients including iron, folate, vitamin A, and vitamin C increased significantly across quartiles of fiber consumption; and mean calcium intake also increased. In a review article, Lairon concluded that fiber-rich foods also have a number of bioactive phyto-chemicals that may have an additional beneficial role [12]. We analyzed the dietary quality of popular dietary plans and concluded that patients can lose weight with most dietary plans in the short term, but when the goal is to change the lifestyle and maintain changes, it is important to consider whether or not the diet is healthful for cardiovascular concerns over the long-term [57]. This is especially true for patients with metabolic syndrome. Our findings suggest that the highest fiber diets were the best in terms of diet quality.

By focusing on a single aspect of diet - increasing dietary fiber - patients may choose foods of higher dietary quality (whole grains, fruit, vegetables, legumes) without feeling overwhelmed by the complexity of multiple dietary changes. Increased dietary quality and fiber intake were inversely association with body weight in previous studies ([10-12,58]. Our preliminary work reveals that increases in fiber may be associated with changes in other aspects of diet (e.g., reducing saturated fat intake), thereby affecting dietary quality even beyond the simple increase in fiber intake. We concluded from our pilot study that it may not be necessary to give instruction on several areas of the diet because correct simple changes might beneficially influence other areas of diet [39]. Simplifying diet changes, increasing fiber intake appears to have excellent effects on weight and factors of the metabolic syndrome.

## Conclusion

Data from the present study will enhance our understanding of the overall impact of a simple dietary change on metabolic health and diet. If the simple fiber approach is successful, it may then be used to develop a simple public health message.
